##### Implanted loop recorder

The Medtronic Reveal LINQ ILR (Medtronic, Minneapolis, MN, USA) will be used to monitor and assess patients’ heart rhythm. The device is highly sensitive and programmable to detect the occurrence of AF and AT lasting ≥ 30 s [54, 55]. Programming parameters of the device are summarised in Table 2.

**Table 2 Tab2:** Programming parameters for Reveal LINQ™ implantable loop recorder

Programming feature	Parameter programmed	Duration
Indication	After AF ablation	
AT/AF	Both ‘on’	
AT	Rates ≥ 100 /minutes	
Tachycardia	> 162 /minutes	48 beats
Asystole	4.5 s	
Bradycardia	< 40/min	8 beats
Patient symptom capture	7.5 min	4 episodes

*AF* Atrial fibrillation, *AT* Atrial tachycardia

The patients are registered on the Medtronic CareLink® Network following ILR insertion and instructed on how to perform manual data downloads using their home monitoring equipment. Data from the ILRs are uploaded to the CareLink® server over mobile phone networks. Patients are asked to perform manual data downloads once per week or more frequently, depending on the burden of collected data in individual cases.

Named study team members are granted access to the CareLink® Network server to monitor ILR data uploads for their patients. A dedicated cardiac physiologist, blinded to treatment allocation, analyses downloaded data on a regular basis to produce monthly heart rhythm assessment reports for each patient. A panel of three experts is nominated to adjudicate in cases where heart rhythm is assessed as ambiguous by the cardiac physiologist.

#### Follow-up schedule

Details of the assessments during study participation are given in Fig. 2 as per SPIRIT 2013 recommendations. Recurrence of symptomatic AF during the blanking period (up to 3 months following ablation) will be treated with DC cardioversion with or without use of AADs, depending on patient tolerance and comorbidities. Patients will be offered percutaneous catheter ablation if the AF recurs at a later point in the follow-up period as shown in Fig. 1.

### Data

#### Data collection and management

Source data worksheets and electronic case report forms (eCRFs) have been designed with input from the chief investigator (CI), principal investigator, study statistician and relevant co-applicants. Paper source data worksheets will be used for each patient to collect appropriate study data, and these will then be transcribed into the eCRF database. Trained individuals at each trial centre are named on the delegation of duties log as responsible for data collection and entry on the eCRF. Source data worksheets will be reconciled at the end of the trial with patients’ NHS medical notes in the recruiting centre.

The InferMed MACRO® database system (Elsevier, Amsterdam, the Netherlands) was used to create the eCRF, and it will be used to manage anonymised study data. It has programmable referential data rules and range checks to ensure data integrity at the time of data entry. Any data edits can be monitored through database audit trails, and the security is enforced by individual logins and passwords. This system is hosted and maintained on a secure dedicated server by the King’s Clinical Trials Unit.

#### Adverse events/serious adverse events

All adverse events (AEs) occurring during the course of the trial will be collected, documented and recorded by the research team at each trial centre. Patients are advised to contact the research team if they have any health concerns during the study follow-up and will be prompted to report those at every study visit.

The research teams will ensure that known complications as well as unexpected events/reactions are detailed in patients’ study files as well as their medical notes. The teams will follow an agreed protocol for timely reporting of serious adverse events (SAEs), which involves written notification to the chief investigator and the study sponsor as soon as possible. A list of expected complications of the ablative procedures is shown in Table 3.

**Table 3 Tab3:** Known complications associated with ablative procedures in Catheter Ablation versus Thoracoscopic Surgical Ablation in Long Standing Persistent Atrial Fibrillation study

Adverse events	Serious adverse events
Bruising, hematoma, vascular injury not requiring intervention	Vascular complications requiring blood transfusion or intervention
Pericardial/pleural effusion (observation only)	Symptomatic pericardial/pleural effusion or requiring intervention
Broken rib	Stroke/transient ischemic attack
Pneumothorax requiring observation	Pneumothorax requiring chest drain
Infection (i.e., pneumonia)	Empyema
Pulmonary oedema	Myocardial infarction
Temporary phrenic nerve damage	Permanent phrenic nerve damage
Pain near surgical sites	Pulmonary vein stenosis (> 50% reduction in diameter from baseline)
	Requirement to insert PPM (with or without prior conduction tissue damage)
	Cardiac trauma requiring surgical intervention
	Radiation-induced skin damage
	Oesophageal atrial fistula
	Death

*PPM* Permanent pacemaker

Recurrence of AF and subsequent hospital admission for DC cardioversion or percutaneous catheter ablation will not be treated as SAEs in the trial, but will be recorded and reported with the results.

### Data from imaging modalities and questionnaires

cMRI will be performed during the baseline visit and again at 6 months after the ablation. It will be used to capture LA area and length [56, 57] and to calculate maximum and minimum LA volumes as well as the cross-sectional diameter of PVs. The images will be acquired using planes in the LV long- and short-axis stacks. A specific protocol of sequences for late gadolinium enhancement (LGE) of the LA will be used to evaluate location and quantification of LA scars [58]. The LV function will also be measured by volume quantification in systole and diastole using endocardial tracing [59–61].

TTEs will be performed at baseline, 3 months after the ablation and at the last study visit (12 months after the ablation). In addition to the standard clinical protocol set out by British Society of Echocardiography, we will acquire images to allow for offline assessment of LA function (measurement of myocardial velocities, LA strain and strain rate) by using tissue Doppler and 2D speckle-tracking methods [62–64].

The EHRA symptoms score and AFEQT and EQ-5D-5L questionnaires will be used at each study visit to assess any changes in patients’ symptoms and quality of life from baseline to the end of the follow-up period [39, 65, 66]. We have also designed a health economics questionnaire to collect patient-reported data on the use of primary, secondary and community health and social care services following ablation to estimate costs.

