#### Treatment allocation

Patients with confirmed eligibility for participation at baseline assessments will proceed to being assigned to treatment group by computer-generated sequence in a 1:1 ratio using minimisation. A secure 24-h bespoke web-based system hosted by the King’s Clinical Trials Unit provides named research team members with access to the allocation system where they enter each participant’s unique participant identification number, initials and date of birth in an electronic online form. In addition, the system uses the study site code, participant’s sex and the size of the left atrium (< 50 mm, > 50 mm) as stratifying variables. Allocation is concealed, but blinding is not possible in this trial. However, the primary outcome assessor will be blinded to treatment arms.

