#### Ablation procedures

##### Thoracoscopic surgical AF ablation

Details of the operation have been described previously by Yilmaz and others [45–47]. In this trial the protocol additionally mandates the presence of a cardiac electrophysiologist in theatre during surgical ablation to ensure that conduction block is tested and achieved for all lesions, because this has been associated with a trend towards better outcomes [48]. Cardiac surgeons participating in this study need to be experienced in video-assisted thoracoscopic surgery and to have conducted at least 20 thoracoscopic ablations for AF as the primary operator.

Transoesophageal echocardiography (TOE) will be performed with the patient under general anaesthesia to exclude left atrial (LA) thrombus prior to the start of the procedure. Three thoracoports will be introduced on each side. Pulmonary veins (PVs) and LA antrum will be exposed by pericardiotomy and blunt dissection using a Lumitip™ dissector (AtriCure, Inc., West Chester, OH, USA) into the transverse and oblique sinuses. Pulmonary vein isolation (PVI) will be performed from the epicardial surface using a bipolar radiofrequency ablation clamp (AtriCure, Inc.) and overlapping applications around the LA antrum. PVI will be confirmed at the end of the procedure by testing for entrance and exit block during pacing on both sides of the lesion in SR. Further ablation will be performed if PVI is incomplete. An Isolator multifunctional pen (AtriCure) will then be used to ablate ganglionic plexi located by high-frequency stimulation. Additional linear lines will be undertaken using the multifunctional pen (AtriCure) connecting the contralateral superior PVs (roof line) and the inferior PVs (inferior line) to create a posterior wall box lesion. If AF persists, the SR will be restored by external DC cardioversion. Sensing and pacing manoeuvres will then be used to verify electrical isolation of the posterior box in SR. The LAA will then be excluded using the AtriClip® LAA excluder system (AtriCure) owing to recent emerging evidence of improved outcomes with LAA exclusion mechanically and electrical isolation [49–52]. The ILR will be implanted at the end of the procedure, and patients will be extubated in the operating theatre.

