### Monitoring

An independent data monitoring committee (DMC) consisting of four members (two cardiologists, a surgeon and a statistician) has been established, with functions and responsibilities detailed in a DMC charter. The DMC meets at least twice annually and communicates their advice to the trial steering committee (TSC).

The TSC has executive power and consists of seven members, five of whom are independent (two cardiologists, one surgeon and two lay members). This committee will meet twice annually for the duration of active patient recruitment and follow-up, and additional ad hoc meetings may also be scheduled if necessary. This group’s functions and remit are defined in the TSC charter. Two external independent groups of experts specialising in electrophysiology, cardiology and thoracic surgery will be formed to evaluate primary and safety endpoints of the trial.

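### The article rules out blinding for everyone but the primary outcome assessor, which is too broad for the atrial imaging outcome, whose readers could be masked at low cost

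*Protocol article*

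**What the plan says.** All locations are in the protocol article.

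- **Treatment allocation.** A general statement, "Allocation is concealed, but blinding is not possible in this trial", is followed by one exception: "However, the primary outcome assessor will be blinded to treatment arms".
- **Implanted loop recorder.** This section shows who that assessor is: "A dedicated cardiac physiologist, blinded to treatment allocation, analyses downloaded data on a regular basis". Statistical analyses confirms that a single blinded physiologist identifies the arrhythmia-free patients.
- **Monitoring.** Two external expert groups "will be formed to evaluate primary and safety endpoints of the trial". Imaging outcomes are not in their remit, and the section does not say whether these groups are masked.
- **Outcomes, Secondary.** Change in atrial size and function on echocardiography and cardiac MRI is a declared secondary outcome.
- **Data from imaging modalities and questionnaires.** Echocardiography is done at baseline, 3 and 12 months, and "we will acquire images to allow for offline assessment of LA function (measurement of myocardial velocities, LA strain and strain rate" by tissue Doppler and speckle tracking. Cardiac MRI is done at baseline and 6 months. It captures LA area and length, is used to "calculate maximum and minimum LA volumes as well as the cross-sectional diameter of PVs", and quantifies LA scar on late enhancement. Nothing is said about masking the readers to arm or visit.
- **Statistical analyses.** Continuous data are compared by t test or Mann-Whitney test at P < 0.05.

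**The concern.** The article takes a position on blinding instead of leaving it open. Its general statement covers the imaging readers, and none of its stated safeguards reaches them. For patients and operators the statement is plainly right. For someone who later measures strain or volume on a recorded image it is not, because the image can be separated from the allocation.

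The measurements depend to some degree on the reader, and the primary hypothesis favours surgery. Baseline assessments come before allocation and the follow-up scans come after it. If scans are read as they arrive, only the follow-up reading can be influenced by knowledge of the arm, and any shift passes straight into the change score. Neither a t test nor a Mann-Whitney test can tell such a shift from a treatment effect.

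**Working it through.** **1. Which roles the article covers**

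- Patients and operators: covered by the general statement, and masking is not feasible.
- Loop-recorder physiologist: the stated exception, masked.
- External groups for primary and safety endpoints: independent, masking not stated.
- Echocardiography and MRI readers: covered by the general statement and by no exception, although echocardiographic LA function is read offline.

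That the imaging readers are unmasked follows from a general statement with a single exception. No section says it outright.

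**2. Patients per arm, starting from the plan's own figure**

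Inputs from Statistical analyses: 76% v 44%, 90% power, 5% significance (taken as two-sided), 25% margin including 10% dropout. With the pooled-variance formula, no continuity correction and mean proportion 0.60:

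n = [1.960·√(2·0.60·0.40) + 1.2816·√(0.76·0.24 + 0.44·0.56)]² / 0.32² = (1.358 + 0.839)² / 0.1024 = 47.1, so 48 per group.

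48 × 1.25 = 60 per group, 120 in total. The plan's figures reproduce. With 10% dropout, 60 × 0.90 = 54 per arm. I use 54 for imaging on the assumption that missing scans follow the general dropout rate.

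**3. Effect of a reading shift**

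The documents give no SD, target difference or reader error for any imaging measure, so the shift is an assumption. Let unmasked reading add a difference of b SD between arms, with no true difference and equal SDs. The two-sided 5% test then rejects with probability

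Φ(b·√(n/2) − 1.96) + Φ(−b·√(n/2) − 1.96).

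For n = 54, √(n/2) = 5.196:

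| Assumed shift b (SD) | b·√(n/2) | False-positive rate, 54 per arm | False-positive rate, 60 per arm |
|---|---|---|---|
| 0 | 0 | 5.0% | 5.0% |
| 0.1 | 0.52 | 8.1% | 8.5% |
| 0.2 | 1.04 | 18.0% | 19.5% |
| 0.3 | 1.56 | 34.4% | 37.6% |

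**4. Scale**

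With 54 per arm, the difference detectable with 80% power is (1.960 + 0.842)·√(2/54) = 0.54 SD. A shift of 0.2 to 0.3 SD would be roughly 37% to 56% of that (0.2/0.54 and 0.3/0.54).

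**5. Arm and visit are different matters**

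Only knowledge of the arm creates a difference between arms directly. Knowledge of the visit, if it acts equally in both arms, distorts the change within each arm but largely cancels in the comparison.

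**The case against.** The strongest objection is that this is inferred from what is not said. The blinding sentence stands under Treatment allocation, does not contain the word only, and does not mention imaging readers. A condensed article may leave image handling to a full protocol or imaging manual, which could provide for masked reading. It therefore cannot be claimed that the readers are in fact unmasked. What survives is narrower: the article makes a trial-wide statement about blinding, names one exception, and the statement is too broad for this outcome.

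Second, masking would be incomplete. In the surgical arm, "The LAA will then be excluded using the AtriClip® LAA excluder system (AtriCure" and so on; no such step is described for catheter ablation. The mitral isthmus line is described only for catheter ablation. The clip, or the scar pattern on MRI, may therefore reveal the arm. Patients enter in long-standing persistent fibrillation, so sinus rhythm at follow-up may reveal the visit. The article does not discuss image appearance, so these are inferences, but reasonable ones. They reduce the gain without removing it.

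Third, the percentages are the power curve of a two-sample test applied to an assumed shift. They show what a bias of that size would do, not that one exists. This stands.

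Three stronger readings are tempting and not supported:

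- *That all atrial measures are traced by hand offline.* The article uses offline only for LA function on echocardiography, and tracing only for left ventricular function. How far the MRI atrial measures depend on the reader is not stated.
- *That clipping the appendage lowers LA volume mechanically in one arm.* This depends on whether the appendage is included in the measurement, which is not stated. It concerns measurement definition, which masking would not change, and forms no part of this point.
- *That the trial's main result is at risk.* The loop-recorder data are read by a masked physiologist.

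**Conclusion.** The point holds in limited form. The statement that blinding is not possible, excepting only the primary outcome assessor, is broader than it needs to be. As written it leaves the readers of a declared secondary outcome unmasked, although at least the echocardiographic LA function measures are read offline, where masking is feasible. That MRI area, length, volumes and scar can be handled in the same way is my inference from their being image measurements.

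The size of any bias is unknown. On the stated assumptions (a constant shift of 0.1 to 0.3 SD, 54 per arm, no true difference, two-sided 5% test), the false-positive rate would be about 8% to 34% instead of 5%. The consequence is confined to atrial size and function. The primary outcome, its sample size and its analysis are unaffected. The change is worth making because it is cheap, not because bias has been shown.

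**What to change.** - Under Treatment allocation, limit the statement that blinding is not possible to patients and operators.
- In the imaging section, state that the planned readers measure stored echocardiography and MRI images with arm, patient identity and visit date removed, and with baseline and follow-up studies in random order.
- Report with the results where the clip, scar pattern or rhythm may have revealed the arm or the visit.
- If a full protocol or imaging manual already provides for masked reading, say so and bring the article's statement into line.

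This takes a few sentences of text and the coding of image files. It needs no additional reader, scan or patient. The downside is the file handling, some delay if images are pooled so that they can be read in random order, and masking that remains partial on follow-up images.

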### Monitoring

An independent data monitoring committee (DMC) consisting of four members (two cardiologists, a surgeon and a statistician) has been established, with functions and responsibilities detailed in a DMC charter. The DMC meets at least twice annually and communicates their advice to the trial steering committee (TSC).

The TSC has executive power and consists of seven members, five of whom are independent (two cardiologists, one surgeon and two lay members). This committee will meet twice annually for the duration of active patient recruitment and follow-up, and additional ad hoc meetings may also be scheduled if necessary. This group’s functions and remit are defined in the TSC charter. Two external independent groups of experts specialising in electrophysiology, cardiology and thoracic surgery will be formed to evaluate primary and safety endpoints of the trial.

### Statistical analyses

All statistical analyses will be based on intention to treat, and the data analysed will be derived from all randomised participants. We will also perform sensitivity analyses to explore the impact of missing data, non-compliance and withdrawals. R statistical software version 3.0.2 (or later; R Foundation for Statistical Computing, Vienna, Austria) will be used to analyse data.

Sample size (*n* = 120) was calculated on the basis of data derived from our pilot study showing freedom for AF/AT at 6 months in the surgical group in 76% versus 44% in the catheter group. Using these results a sample size of 48 per group will be required to detect a difference in the primary outcome with 90% power and a 5% significance level. There is a margin of error of 25%, which includes a 10% dropout rate.

The primary outcome of the trial is the proportion of patients with LSPAF undergoing ablation who are free from atrial arrhythmias (defined as a single episode of ≥ 30 s) within 1 year after a single ablation procedure. ‘Arrhythmia-free’ patients will be identified through ILR data assessments performed monthly by a single blinded cardiac physiologist. Chi-square tests will be used for comparisons between the trial arms. A logistic regression model will be developed to estimate the probability of being free from AF at 1 year by either procedure. The primary measure to be reported is the OR of being ‘AF-free’ for the surgical group after the other factors in the model have been controlled for. The recurrence of AF and duration of AF freedom will be analysed using Kaplan-Meier survival curves.

Binary secondary outcomes (reduction in arrhythmia burden, freedom from arrhythmia following multiple procedures) will be analysed in the same manner as the primary outcome using a combination of chi-square tests and logistic regression. Freedom from arrhythmia following multiple procedures will be analysed using Kaplan-Meier survival curves.

Continuous data will be analysed using either Student’s *t* test or the Mann-Whitney *U* test and presented as mean ± SD, mean (95% CI) or median (IQR), depending upon distribution of obtained data. *P* < 0.05 will be considered significant.

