**Methods/design:**

Catheter Ablation versus Thoracoscopic Surgical Ablation in Long Standing Persistent Atrial Fibrillation (CASA-AF) is a prospective, multi-centre, randomised controlled trial within three NHS tertiary cardiovascular centres specialising in treatment of atrial fibrillation. Eligible adults (*n* = 120) with symptomatic, long-standing, persistent atrial fibrillation will be randomly allocated to either catheter ablation or thoracoscopic ablation in a 1:1 ratio. Pre-determined lesion sets will be delivered in each treatment arm with confirmation of appropriate conduction block. All patients will have an implantable loop recorder (ILR) inserted subcutaneously immediately following ablation to enable continuous heart rhythm monitoring for at least 12 months. The devices will be programmed to detect episodes of atrial fibrillation and atrial tachycardia ≥ 30 s in duration. The patients will be followed for 12 months, completing appropriate clinical assessments and questionnaires every 3 months. The ILR data will be wirelessly transmitted daily and evaluated every month for the duration of the follow-up. The primary endpoint in the study is freedom from atrial fibrillation and atrial tachycardia at the end of the follow-up period.

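### Continuous change outcomes are tied to unadjusted t or Mann-Whitney tests, apparently chosen on the observed distribution; one prespecified baseline-adjusted model per outcome would be more precise and would fix the effect measure

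*Protocol article*

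**What the plan says.** The Statistical analyses section of the protocol article gives one rule for every continuous outcome: "Continuous data will be analysed using either Student’s *t* test or the Mann-Whitney *U* test". The same sentence lists mean with SD, mean with 95% CI, or median with IQR as possible summaries, "depending upon distribution of obtained data". It names no covariate and no model for repeated visits, and does not say whether follow-up scores or changes are compared.

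The outcomes it governs all have a baseline value. The Secondary outcomes section defines the atrial measures and the symptom and quality-of-life scores as changes. The section on imaging and questionnaires speaks of symptoms and "quality of life from baseline to the end of the follow-up period".

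Schedules differ by measure:
- questionnaires: baseline, then 3, 6, 9 and 12 months;
- transthoracic echocardiography (TTE): baseline, 3 and 12 months;
- cMRI: baseline and 6 months.

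Elsewhere the article does plan adjusted models. The primary and binary secondary outcomes get logistic regression, and the Health economic analysis adjusts QALYs and costs for baseline EQ-5D-5L.

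**The concern.** When an outcome has a baseline measurement, a plain two-sample test on follow-up or change scores usually leaves precision unused. Regressing the follow-up value on baseline and arm (ANCOVA) estimates the same mean difference with a variance that, in large samples, is never greater. The trial is sized for its binary primary outcome only, so quality of life and atrial function must be read with whatever precision that sample gives.

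The second issue is the choice of test. A t test concerns a difference in means and a Mann-Whitney test concerns ranks. If the observed distribution decides between them, the quantity being estimated is not known in advance and may differ between outcomes, or between visits of one outcome. Reporting medians with IQRs also describes each arm without committing to an interval for the difference between arms.

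**Working it through.** **The plan's own figure.** The protocol gives no sample-size figure for continuous outcomes. For the primary outcome it cites pilot data "showing freedom for AF/AT at 6 months in the surgical group in 76% versus 44% in the catheter group" and concludes: "a sample size of 48 per group will be required to detect a difference in the primary outcome with 90% power and a 5% significance". With pooled variance, two-sided and without continuity correction:

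n = [1.960·√(2·0.60·0.40) + 1.282·√(0.76·0.24 + 0.44·0.56)]² / 0.32² = (1.358 + 0.839)² / 0.1024 ≈ 47.1, rounded up to 48. This reproduces.

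The protocol adds: "There is a margin of error of 25%, which includes a 10% dropout rate". 96 × 1.25 = 120, split 1:1. Taking off the stated 10% dropout leaves 120 × 0.9 / 2 = 54 per arm, used below.

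**Assumptions not in the protocol.** These are the correlation r between baseline and follow-up (range 0.3 to 0.8), equal SDs at both times and in both arms, a true difference of 0.5 SD for the power figures, and two-sided 5% tests.

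**Variance factors relative to SD².** Follow-up score only: 1. Change score: 2(1 − r). ANCOVA: 1 − r². The relative CI width is the square root of the ratio, for example √(0.60/0.51) = 1.08 for change at r = 0.7 and √(1/0.51) = 1.40 for follow-up only.

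| r | ANCOVA factor | Change factor | CI wider than ANCOVA: change | CI wider than ANCOVA: follow-up only | Power: change | Power: follow-up only | Power: ANCOVA |
|---|---|---|---|---|---|---|---|
| 0.3 | 0.91 | 1.40 | 24% | 5% | 59% | 74% | 78% |
| 0.5 | 0.75 | 1.00 | 15% | 15% | 74% | 74% | 85% |
| 0.7 | 0.51 | 0.60 | 8% | 40% | 92% | 74% | 95% |
| 0.8 | 0.36 | 0.40 | 5% | 67% | 98% | 74% | 99% |

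In effective sample size, a change-score test keeps 65%, 75%, 85% and 90% of what ANCOVA would give. A follow-up-only test keeps 91%, 75%, 51% and 36%.

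The difference detectable with 80% power is (1.96 + 0.84)·√(2v/54), where v is the variance factor. At r = 0.5 it is 0.54 SD for either t test (v = 1) and 0.47 SD for ANCOVA (v = 0.75). At r = 0.7 it is 0.42 SD for change (v = 0.60) and 0.39 SD for ANCOVA (v = 0.51).

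These factors ignore the few degrees of freedom spent on covariates, which matter little at this size. They describe the t test. No equivalent figure for Mann-Whitney can be had without assuming a distribution.

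**Choosing the test on the data.** A simulation with 54 per arm and 10,000 runs applied a Shapiro-Wilk check and then a t or Mann-Whitney test. The rejection rate under no difference was 4.7% for normal data and 4.9% for skewed data.

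**The case against.** Several stronger readings are tempting, and the protocol does not support them.

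- **That the baseline is thrown away.** The outcomes are worded as changes, and a test on a change score uses the baseline, though less efficiently than ANCOVA. The analysis sentence simply does not say which score is tested.
- **That the loss is always large.** On change scores it is modest once r reaches 0.7. It is large only for change scores at low r or for follow-up scores at high r.
- **That the comparison is biased.** Under randomisation, comparisons of follow-up or change scores are both unbiased, and chance baseline imbalance is already reflected in the standard error.
- **That choosing the test on the data inflates type I error.** The simulation shows no such inflation. The phrase about distribution might also govern only the presentation of results, although its natural reading covers the test.
- **That every outcome is measured each quarter.** Only the questionnaires are.
- **That EHRA is wrongly given a t test.** The sentence concerns continuous data and never assigns EHRA a test. Mann-Whitney is on the list and suits an ordinal class.
- **That the plan contradicts its own QALY analysis.** Baseline EQ-5D-5L enters the area under the curve directly, so adjustment there has its own rationale.

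It can also be said that covariates and repeated-measures models are normally left to an analysis plan, which is not shown here. That would answer a complaint of omission. It does not answer this one, because the article names the tests outright and an analysis plan consistent with it would inherit them.

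**Conclusion.** The point holds in a limited form. The protocol fixes unadjusted two-sample tests, apparently selected on the obtained data, for secondary outcomes defined as changes from a collected baseline. The loss is precision and an effect measure not settled beforehand.

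Under the likelier change-score reading, the precision penalty against ANCOVA falls from 24% to 5% in CI width as r rises from 0.3 to 0.8. Under the follow-up-only reading it rises from 5% to 67%. All of these figures rest on the assumed r and equal SDs. What does not depend on r is the direction: in large samples ANCOVA is at least as precise as either alternative. The primary outcome is untouched.

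**What to change.** Replace the sentence on continuous data with one prespecified baseline-adjusted model per outcome. Include the minimisation factors (site, sex, left atrial size) as covariates and report the adjusted mean difference with its 95% CI:

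- **cMRI measures:** ANCOVA at 6 months.
- **AFEQT and EQ-5D-5L:** ANCOVA at 12 months, or a mixed model over 3, 6, 9 and 12 months with the 12-month difference named as the reported contrast.
- **TTE measures:** ANCOVA at 12 months, or a mixed model over 3 and 12 months.
- **Skewed residuals:** keep the same model and take a bootstrap CI; do not switch test.
- **EHRA class:** an ordinal model adjusted for baseline class is an option, not a requirement.

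The cost is protocol and analysis-plan wording. All the data needed are already scheduled for collection. The change should be made before outcome data are examined by arm.
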